**PROTOCOL SUMMARY**

**1.1. Synopsis**

Version Date: June 25, 2025 (v3.0)

Page **7** of **54**

**Title:**

**Magnesium in acute pediatric asthma in the emergency department (MAGICIAN) - a multicentre randomized controlled clinical trial protocol**

**Study Description:**

This is a multi-centre, double blind, randomized controlled trial of intravenous magnesium in children with asthma or probable asthma. The purpose of this study is to find out if children who are given intravenous magnesium (IVMg) for refractory asthma/wheezing have a greater improvement in breathing discomfort compared to no magnesium. This protocol has not yet generated results.

We hypothesize that children between the ages of 2.00-17.99 with a Pediatric Respiratory Assessment Measure (PRAM) Score ≥ 5 that are given IVMg will have a mean PRAM improvement at 120 minutes post IVMg ≥1.0 point greater compared to placebo

**Objectives:**

Primary Objective:

- In children 2.00-17.99 years old who present to EDs with acute asthma and have persistent moderate-severe asthma after initial optimal standardized therapy, is there a greater reduction (improvement) in the PRAM score at 120 minutes post-intervention start in those given IVMg compared to placebo?

Secondary Objective:

Between these treatment modalities:

1. Is there a difference in the hospitalization rate for asthma at the index ED visit?
2. Is there a difference in the hourly changes in the PRAM, respiratory rate, heart rate oxygen saturation and blood pressure from the pre-intervention baseline to 180 minutes?
3. Is there a difference in the area under the receiver operating characteristic curve for PRAM within 120 minutes?
4. Is there a difference in the proportion of children achieving PRAM indicating mild asthma status, i.e. ≤ 3 points (widely accepted criterion for discharge home) at 120 minutes?
5. Does the treatment effect on the primary outcome vary between subgroups defined by: age, sex, pre-randomization PRAM, atopy, non-rhinovirus nasal pathogen36 and “viral- wheeze” phenotype?

[figure not shown]

Enrollment closure: Winter 2027-2028, Analyses: Spring 2028

**MAGICIAN** Clinical Trial Protocol

Version Date: June 25, 2025 (v3.0)

Page **8** of **54**

1. Is there a difference in the hospitalization rate for asthma within 72 hours of ED discharge?
2. Is there a difference in the rate of unscheduled visits for asthma within 72 hours of ED discharge?
3. Is there a difference in the overall hospital length of hospital stay?

i) Is IVMg a cost-effective treatment option?

**Endpoints:**

Primary endpoint: PRAM score at 120 minutes post start of experimental therapy.

Secondary endpoints: PRAM, oxygen saturation, heart rate and resp rate 30, 60, 120, 180 minutes and blood pressure 10, 20, 30, 60, 120, 180 minutes after start of experimental therapy and unscheduled medical re-visits/hospitalizations for asthma 72 hours after ED discharge home.

**Study Population:**

192 children, ages 2.00-17.99 years, with a diagnosis of asthma or probable asthma presenting to the Emergency Department (ED) with a PRAM score ≥5 after receiving standard of care treatment for asthma.

**Phase:**

Phase III

**Description of Study Intervention:**

Two groups will be compared. One group will receive intravenous Magnesium and the other group will receive an intravenous placebo (salt water solution not containing magnesium) over 30 minutes.

**Study Duration:**

**Participation Duration:**

72 hours (~3 hours in the emergency department and then a brief email/telephone call ~72 hours later)

[figure not shown]

[figure not shown]

[figure not shown]

[figure not shown]

[figure not shown]

[figure not shown]

[figure not shown]

**MAGICIAN** Clinical Trial Protocol

**1.2. Schema**

**Triage Registered Nurse (RN):** Arrival PRAM score (**see Appendix B (PRAM Score)**)

Moderate to severe disease:

Assessment by ED physician Systemic corticosteroids

Initial therapy with 3 treatments with salbutamol & ipratropium (as per site drug dosing and ipratropium indications) over about 1 hour

Study nurse notified

**Study Nurse measures eligibility PRAM at end of initial therapy, if ≥ 5:** assesses eligibility (If eligibility PRAM is < 5, subject is ineligible for study)

If eligible, **Study Nurse** obtains informed consent

IV start, infusion of IV Normal Saline (NS) bolus as per site standard of care

**Study Nurse** retrieves next appropriate randomized treatment kit from research fridge/pharmacy department

**ED/Study Nurse** infuses experimental solution over 30 minutes

**Experimental Group Treatment**

**IV Mg sulfate** (**wt ≤33 kg: 75 mg/kg; >33 kg: 2,500 mg)**

**Control Group Treatment IV Normal Saline**

**Study Nurse** measures PRAM, RR, HR, BP, O2 sat @ Baseline (pre experimental Rx), BP@ 10’,20’,30’after start of experimental Rx), and PRAM, RR, HR, BP, O2 sat @ 30’,60’, 120’, 180’

Further bronchodilator/other therapy as clinically indicated after experimental infusion finished.

Disposition decision by ED MD

Electronic/paper health chart review and telephone/email follow-up at 72 hrs (+7days)

Version Date: June 25, 2025 (v3.0)

Page **9** of **54**

[figure not shown]

**MAGICIAN** Clinical Trial Protocol

**1.3. Schedule of Activities (SoA)**

The following schedule of activities are to be completed for each participant.

Footnote:

* Consent must take place before any study activities start.

† Only participants who are discharged from the ED are contacted to complete the survey.

Version Date: June 25, 2025 (v3.0)

Page **10** of **54**

Procedures

**Screening/Eligibility**

**Baseline (Pre-Intervention)** (Measurements completed as close to before giving intervention)

**Time Point 0** (administer intervention)

**Time Point 1 (Assessment 1)**

(10 minutes +/- 5 minutes)

**Time Point 2 (Assessment 2)**

(20 minutes +/- 5 minutes)

**Time Point 3 (Assessment 3)**

(30 minutes +/- 5 minutes)

**Time Point 4 (Assessment 4)**

(60 minutes +/- 15 minutes)

**Time Point 5 (Assessment 5)**

(120 minutes +/- 15 minutes)

**Time Point 6 (Assessment 6)**

(180 minutes +/- 15 minutes))

**Follow-Up** (72 hours after discharge - up to 7 days post ED discharge)

Informed Consent

X*

Demographics

X

Medical History

X

Randomization

X

Administer Study Intervention

X

Concomitant medication review

X

X

X

X

PRAM Score

X

X

X

X

X

X

Respiratory Rate

X

X

X

X

X

Heart Rate

X

X

X

X

X

Blood Pressure

X

X

X

X

X

X

X

O2 saturation

X

X

X

X

X

Survey

X†

Adverse Event review and evaluation

X

X

X

X

X

X

X

Complete Case Report Forms (CRFs)

X

X

X

X

X

X

X

X

[figure not shown]

**MAGICIAN** Clinical Trial Protocol

**2.**

**INTRODUCTION**

**2.1.** **Study Rationale - The Need For A Trial**

Acute asthma exacerbations are a leading cause of pediatric emergency department (ED) visits and hospitalizations.1,2 Despite receiving optimal initial treatment with inhaled salbutamol, ipratropium and systemic corticosteroids (CS), 50% of the children with severe acute asthma experience ongoing moderate-to-severe respiratory distress.3 In this refractory population, which accounts for 84% of asthma hospitalizations, guidelines recommend intravenous magnesium (IVMg).4-9 However, IVMg therapy is resource- intensive as it demands close monitoring by specialized pediatric ED nurses, requires IV insertion, and can cause hypotension.10 To minimize these concerns, we evaluated the benefits of nebulized Magnesium (Mg) in a 7-centre Canadian CIHR-funded Randomized Controlled Trial (RCT) (MAGNUM) in this population.3 MAGNUM identified no benefits of inhaled Mg compared to placebo (**Appendix A**).3

There is highly limited and disparate evidence of benefit for IVMg in children, requiring further evidence to justify its continued use.11,12 Early evidence from 2 small single- center placebo-controlled pediatric RCTs (total N=61) suggested hospitalization benefit,13,14 while a third study reported no benefit (N=54).15 The most-recent Cochrane review based on these 3 studies expressed lack of confidence in the evidence prompted by a more appropriate re-analysis which yielded lack of IVMg effect on hospitalizations.16 Similar conclusion was reached by another review.17 Recent large observational studies found that IVMg was not associated with improved outcomes.11,18 A U.S-wide PHIS study of 91,000 children with acute asthma showed no association of IVMg with shorter hospital stay, lower initiation, duration of airway support or use of IV salbutamol.19 In a prospective study of pediatric moderate-severe refractory asthma with a propensity score-covariate adjustment, IVMg was associated with a 2-hour worsening

of the Acute Asthma Intensity Research Score, a 6-fold higher odds of hospitalization and no difference in time to every 4 hours salbutamol, an accepted parameter for discharge home, compared to no IVMg.11

These conflicting results may be due to differences in the timing of IVMg administration, confounding, and the choice and the timing of the primary outcome: 1) the early RCTs only measured an immediate IVMg effect on respiratory status;13,14,20-22 there is no evidence of its incremental benefit on outcomes measured at the peak effect of routine key co-interventions with CS and bronchodilators, when hospitalization is usually considered (approximately 4 hours after CS); 2) past RCTs did not employ validated asthma scores; 3) IVMg is usually given after ≥4 hours of unsuccessful ED treatment when most clinicians have already decided to admit, even if there is significant clinical improvement;19 4) children given IVMg have 6-10 times higher odds of hospitalization, in part due to confounding by indication, possible lack of Mg efficacy and physician discomfort with discharge after Mg due to concerns about rebound effects.11,23 In a secondary analysis of MAGNUM where some children required IVMg, we demonstrated that the decision to admit is independent of the presenting asthma severity and clinical response to IVMg,23 suggesting that some hospitalizations may be driven by physician

Version Date: June 25, 2025 (v3.0)

Page **11** of **54**

[figure not shown]

**MAGICIAN** Clinical Trial Protocol

discomfort about discharge after Mg rather than by true clinical Mg efficacy. Therefore, hospitalization does not represent an appropriate primary outcome to assess IVMg efficacy. In contrast, alleviation of respiratory distress is a highly suitable primary outcome, as it is the main reason for IVMg therapy.24

We propose an RCT [MAGnesIum Trial in ACute Asthma In Emergency DepArtmeNt: MAGICIAN trial] to conclusively determine if IVMg alters the asthma exacerbation course: it must be given early, with the improvement in respiratory distress measured at the peak effect of key co- interventions using a valid, discriminative, reproducible and responsive-to-change instrument, the Pediatric Respiratory Assessment Measure **(Appendix B: Pram Score)**.25

Trial results will impact care regardless of whether an association is found. If IVMg is found to decrease respiratory distress, we will use knowledge translation (KT) to implement *routine and early* IVMg therapy for refractory asthma. A negative result will be followed by de-implementation strategies to cease the use of IVMg for refractory asthma which may also lead to cost savings: IVMg therapy is personnel- intensive, requires an IV which may not be necessary in moderate-severe asthma, may cause hypotension,10 and as such greatly augments the odds of hospitalization.11,23

**2.2. Background**

Pediatric asthma guidelines recommend inhaled ß2 agonists, anticholinergics and systemic CS for acute attacks.4-6,8,9,26 However, 50% asthmatics are resistant to ß2 agonists3 and a response to CS may take well above 4 hours.27 In MAGNUM, 49% of screened children remained in moderate-severe distress after initial therapy and 45% were hospitalized.3 These non-responders represent the majority of asthma hospitalizations,25 with high treatment costs.28,29 IVMg sulfate could relieve airway obstruction by multiple mechanisms.30-33 Of the 8 RCTs evaluating IVMg in children, only 3 used a placebo-controlled design (N 31,30,54) assessing lung function/asthma score and hospitalization,13-15 with disparate conclusions. Two positive RCTs excluded preschoolers who constitute the majority of pediatric asthma ED visits34 and failed to use ipratropium for initial therapy,13,14 and the negative study did not limit enrolment to refractory asthma.15 The table below summarizes the pediatric RCTs of IVMg: 3 used non-placebo comparators, 1 did not measure hospitalization21 and 1 had no control group: only 3 small trials were placebo-controlled (shaded lines).

50 mg/kg/hr for 4 hours (max 8 gm IV Mg 50 mg/kg (no

Discharge home within 24 hours.

Clin asthma score at 1 hour Mechanical ventilation

Irazuzta

2015

38

6-18

in 4 hr)

max) over 1 hour IV terbutaline, IV aminophylline None

Singhi

*Torres*

2014

*2012*

100

*143*

1-12 50 mg/kg over 20 min (no max)

*2-15 25 mg/kg over 20 min (max 2 g)*

Version Date: June 25, 2025 (v3.0)

Page **12** of **54**

***Scarfone 2000 54 1-18 75 mg/kg over 20 min (max 2.5 g) Saline placebo*** Pulmonary Index at 2 hours

hospitalization

**Ciarallo 2000 30 6-18 40 mg/kg over 20 min (max 2 g) Saline placebo** PEFR, FEV1, FVC,

hospitalization

**Principal Year N Age IV-Mg Comparative Study Outcomes Author (years) therapy**

[figure not shown]

**MAGICIAN** Clinical Trial Protocol

Gurkan Devi

1999 20

1997 47

6-16 40 mg/kg over 20 min (max 2 g)

1-12 100 mg/kg over 35 min (no max)

Saline placebo Aminophylline

PEFR, vital signs at 1.5 hour PEFR and O2 saturation

PEFR, peak expiratory flow rate; FEV1, forced expiratory volume in 1 second; FVC, forced vital capacity

A review of 61,854 pediatric Emergency Department (ED) asthma visits from the U.S.PECARN registry found that only 26% of children hospitalized for asthma got IVMg in the ED,10 and that IVMg is generally given late (median 154 min).19 In our secondary MAGNUM analysis, IVMg was associated with a 10-fold increase in hospitalizations when adjusted for presenting and post Mg asthma severity,23 suggesting either confounding by indication, lack of Mg efficacy or concern about discharge after Mg due to potential rebound effect **(Appendix C)**. The short IVMg half-life (2-2.7 hrs)35,36 has not been linked to the duration of clinical effect of IVMg.17 Only 1.8% children discharged post IVMg return to the ED vs 3.6% without.10

Equipoise exists for IVMg benefit in refractory pediatric asthma.16 The latest 2016 Cochrane review highlights the limitations of the evidence, especially the small number of participants and disparate results.16 While the fixed-effect analysis of the 3 studies13-15 suggests a large reduction in hospitalizations, a re-analysis with a more appropriate random-effect method yielded lack of significant difference [OR 0.18 (0.02-1.59)] and while the point estimate is low, so was the authors’ confidence in the evidence.16

While IVMg itself is inexpensive, its administration is resource-intensive because of the need for nurses skilled in pediatric ED care and IVMg infusion protocols,37,38 as well as for blood pressure monitoring due to the potential for hypotension.39 Given challenges with IV access in some young children,40-44 ED physicians tend to delay IVMg therapy to avoid the “poke.”39 Clarification of IVMg benefit would provide a much-needed justification for related human and interventional resource use.

In preparation for this study, we conducted a Pediatric Emergency Research Canada (PERC) survey showing that a) alleviation of respiratory distress represents the main reason for IVMg use, b) most ED physicians routinely hospitalize after IVMg, irrespective of asthma severity or Mg response, in part due to lack of solid evidence of improved outcomes after IVMg **(Appendix D: PERN Survey)**.24

**2.3. Risk/Benefit Assessment - Participant Safety**

Mg has a theoretical potential for hypotension, hypopnea and heart block,45 but only hypotension has been reported with any frequency. The IVMg RCT of 1109 adults reported 8% hypotension46 but nobody had Mg stopped for hypotension. Pediatric IVMg trials with Mg doses 75 and 100 mg/kg did not report any hypotension (N=101).15,20 While a review of the PECARN Registry found a median dose 50 mg/kg had a hypotension rate of 6.8%,10 the mean decrease in the systolic pressure was 5 mm Hg, with uncertain clinical significance. No hypotension was observed in 3 pediatric pharmacologic ICU studies of 75 mg/kg IV Mg in children ≤30 kg and 50 mg/kg in those

>30 kg followed by 40 mg/kg/hour for 4 hours.47-49 Two of our participating sites

Version Date: June 25, 2025 (v3.0)

Page **13** of **54**

**Ciarallo 1996 31 6-18 25 mg/kg over 20 min (max 2 g) Saline placebo** PEFR, hospitalization

[figure not shown]

**MAGICIAN** Clinical Trial Protocol

routinely use 75 mg/kg IVMg. A literature review of pediatric status asthmaticus confirms lack of IVMg toxicity.50 Nonetheless, blood pressure will be measured at 10, 20, 30 and 60 minutes and hourly to 180 minutes. If the systolic pressure drops below the 5th percentile-for-age,51 necessary treatment such as IV fluids will be given. Because the children with unstable airway will be excluded and further inhaled salbutamol/other asthma therapies will be given if needed, lack of Mg in the placebo group will not endanger these participants. All study patients will be monitored for 180 minutes post- intervention prior to discharge, to ensure safety. Only 13/723(1.8%) children discharged post IVMg return to the ED vs 1383/38,623(3.6%) without; IVMg is not associated with re-visits.10

**3.**

**OBJECTIVES AND END POINTS**

**Primary question:** In children 2.00-17.99 years old who present to 6 PERC EDs with acute asthma and have persistent moderate-severe asthma after initial optimal standardized therapy, is there a greater reduction (improvement) in the PRAM score at 120 minutes post- intervention start in those given IVMg (75 mg/kg, max 2.5 g), compared to placebo?

**Primary endpoint:** PRAM score at 120 minutes post start of experimental therapy.

**Secondary questions:** Between these treatment modalities:

a)

b)

Is there a difference in the hospitalization rate for asthma at the index ED visit?

Is there a difference in the hourly changes in the PRAM, respiratory rate, heart rate oxygen saturation and blood pressure from the pre-intervention baseline to 180 minutes?

Is there a difference in the area under the receiver operating characteristic curve for PRAM within 120 minutes?

Is there a difference in the proportion of children achieving PRAM indicating mild asthma status, i.e. ≤ 3 points (widely accepted criterion for discharge home) at 120 minutes?

Does the treatment effect on the primary outcome vary between subgroups defined by: age, sex, pre-randomization PRAM, atopy, non-rhinovirus nasal pathogen36 and “viral-wheeze” phenotype?

Is there a difference in the hospitalization rate for asthma within 72 hours of ED discharge?

Is there a difference in the rate of unscheduled visits for asthma within 72 hours of ED discharge?

Is there a difference in the overall hospital length of hospital stay? Is IVMg a cost-effective treatment option?

c)

d)

e)

f)

g)

h)

i)

**Secondary endpoints:** PRAM, oxygen saturation, heart rate and resp rate 30, 60, 120, 180 minutes and blood pressure 10, 20, 30, 60, 120, 180 minutes after start of experimental therapy and unscheduled medical re-visits/hospitalizations for asthma 72 hours after ED discharge home.

Version Date: June 25, 2025 (v3.0)

Page **14** of **54**

[figure not shown]

**MAGICIAN** Clinical Trial Protocol

**Hypothesis:** Based on a two-tailed hypothesis, children with PRAM ≥ 5 after initial therapy given IV Mg will have a mean PRAM improvement at 120 minutes post IVMg ≥1.0 point greater compared to placebo.

**4.**

**STUDY DESIGN**

**4.1. Overall Design and the Scientific Rationale for Study Design**

As mentioned above, previous RCTs of IV Mg in children are small and have methodologic limitations. The most recent systematic review (Griffiths, 2016) concludes there is equipoise about IV Mg benefit. More recent large IVMg studies cast doubt on Mg benefit but these have non-RCT designs. Therefore, we propose a 6-centre randomized, double-blind, placebo-controlled trial. Two groups will be compared: IVMg sulfate and IV0.9% saline placebo. After initial therapy with the systemic CSs routinely used for acute asthma management at a given site, 3 treatments with inhaled salbutamol and ipratropium (indications for ipratropium vary by site),52 eligible patients with PRAM ≥5 **(Appendix B: PRAM Score)** will receive a 30-minute IV infusion of 75 mg/kg of Mg sulfate (maximum 2.5 g) [experimental group] or an identical volume of 0.9% saline [control group]. Outcomes will be measured during the 180-minute observational period in the ED and at 72 hours post ED discharge. Primary outcome will be the PRAM score at 120 minutes after start of experimental therapy.

PRAM: PRAM is a validated 12-point asthma severity score53 which exhibits the most comprehensive measurement properties of all asthma scores54 and has been successfully used as an outcome in major trials.3,55 It is the only score with demonstrated criterion validity, using respiratory resistance as the gold standard.25,53 PRAM has been validated in both preschool and school-aged children in the ED with asthma and has strong association with admission.25 PRAM has inter-rater reliability above 70%25 and is adopted in all pediatric EDs in Canada. Most children treated for acute asthma are preschoolers56 who lack coordination to perform pulmonary function tests reliably. To maximize the accuracy of the PRAM measurement, all study nurses will complete online PRAM training module57 at https://enseignement.chusj.org/PRAM-En. We will use an eligibility cut-off of PRAM ≥ 5 post initial therapy as this is associated with clinically concerning respiratory distress requiring further intervention. PRAM ≥ 5 after one hour of initial care has high accuracy (AUC: 0.88) to predict hospitalization.58 Of the 215 children given IVMg in MAGNUM, 118 had PRAM 5, 41 PRAM 6, 35 PRAM 7 and 21 PRAM ≥8 prior to IV Mg.3

**4.2. End of Study Definition**

A participant is considered to have completed the study if he or she has completed all phases of the study including the last scheduled procedure shown in **Section 1.3(SoA)**.

A participant who is discharged home at the index ED visit will have relevant outcome measures completed by the study nurse up to 180 minutes. These participants will also complete a follow-up questionnaire at approximately 72 hours, at which point their study will be complete.

Version Date: June 25, 2025 (v3.0)

Page **15** of **54**

[figure not shown]

**MAGICIAN** Clinical Trial Protocol

A participant who is admitted to the hospital (e.g transferred from ED to an in-patient unit) will have the study nurse complete any study measures up to 180 minutes. After that, the participant is considered complete. No follow-up will occur 72 hours later.

**5.**

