**8.1.4.**

**Follow-Up**

Participants will receive a follow-up phone call or email (they may state their preference) 72 hours after they are discharged from the ED from the study team.

The study team may attempt to contact participants up to 7 days after discharge to answer the follow-up survey.

If the participant was admitted to the hospital at their index ED visit, they will not be contacted for the follow-up survey.

**9.**

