**9.3. Secondary outcome measures**

The two study groups will also be compared with respect to:

1. Hospitalization for asthma at the index ED visit.
2. Changes in PRAM, respiratory rate, heart rate, oxygen saturation and blood pressure from baseline (pre- intervention) to 30, 60, 120, and 180 min and also in blood pressure to 10 and 20 min post-intervention
3. Area under the receiver operating characteristic curve for the PRAM score changes at 30, 60, and 120 minutes.
4. PRAM denoting mild asthma (≤ 3 points is a widely accepted discharge criterion25) at 120 minutes
5. Hospitalization for asthma at any medical facility within 72 hours post- ED discharge.
6. Unscheduled asthma-related visits to any health care provider within 72 hours post- ED discharge.
7. Hospital length of stay.
8. Open label IVMg administration after the 120-minute measurement of the primary outcome.

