**9.7. Secondary outcomes**

For the continuous outcomes changes in the PRAM, respiratory rate, heart rate and oxygen saturation from pre-intervention to 30, 60, 120, and 180 min, a mixed model repeated measures will be conducted with treatment group as the between factor (IVMg vs placebo) and the within factor time 0,60,120,180 min. The analysis will be repeated with the randomization stratification factors site and age. Similarly, blood pressure will be analyzed with the additional time measures at 10, 20 and 30 minutes. For overall hospital stay, the study groups will be compared using the Wilcoxon ranked-sum test. For binary outcomes (hospitalization, PRAM indicating mild asthma, unscheduled asthma-related re-visits), groups will be compared using the chi-square test. For the analysis of the area under the ROC curve for PRAM scores, a mixed model repeated measures ANOVA will be conducted with the between factor study group (intervention vs placebo) and within factor time (30, 60, 120 minutes). In addition to the omnibus test for the group and time factors, an orthogonal polynomial analysis will be conducted to compare trends over time between the study groups.

A comparison based on a logistic regression analysis will be conducted adjusting for the randomization stratification factors site and age. As the secondary analyses are exploratory, overall significance for them will be set at 0.05 (2-sided).

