**9.9. Safety outcomes**

Each adverse event will be described as per good clinical practice guidelines. Descriptive statistics will be used to report frequencies of adverse events and SAEs in the groups. If appropriate, differences between the groups will be compared using a two-sample t-test or Wilcoxon rank sum test. These analyses will be reviewed by Data and Safety Monitoring Committee (DSMC) every 6 months.

***Missing Data:*** Missing data will be imputed using multiple imputation. Analysis

Version Date: June 25, 2025 (v3.0)

Page **27** of **54**

[figure not shown]

**MAGICIAN** Clinical Trial Protocol

will be done using SAS™ software.

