**10.2.**

**Definition of Serious Adverse Events (SAE)**

Version Date: June 25, 2025 (v3.0)

Page **29** of **54**

[figure not shown]

**MAGICIAN** Clinical Trial Protocol

A Serious Adverse Event is any AE that is:

- fatal

•

•

•

•

•

life-threatening

requires or prolongs inpatient hospital stay

results in persistent or significant disability or incapacity a congenital anomaly or birth defect

an important medical event

The term “life-threatening” in the definition of “serious” refers to an AE in which the participant was at risk of death at the time of the event. It does not refer to an AE that hypothetically might have caused death if it were more severe.

Important medical events are those that may not be immediately life threatening but are clearly of major clinical significance. They may jeopardize the participant and may require intervention to prevent one of the other serious outcomes noted above. Examples of such medical events include allergic bronchospasm requiring intensive treatment in an emergency room or at home, blood dyscrasias or convulsions that do not result in inpatient hospitalization, or the development of drug dependency or drug abuse

**Serious Adverse Event (SAE)** will be documented for any incident that consist of:

1. hypotension below the 5th percentile for age requiring medical intervention within 180 minutes of the start of the experimental therapy, or
2. admission to intensive care unit (ICU) at the index ED visit.
3. admission to intensive care unit (ICU) for asthma within 72 hours after being discharged from ED.

These will be reported to the PI, SickKids REB, local REB and the DSMC.

Since hypotension is the only side-effect of IVMg occurring with appreciable frequency, all enrolled patients will be on precautionary frequent blood pressure monitoring as per the study protocol. If the systolic blood pressure drops below 5th percentile for age, treatment will be given as necessary and DSMC will be notified.

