**10.3.4. Time Period and Frequency for Event Assessment and Follow-Up**

All Adverse Events (AEs) or Serious Adverse Events (SAEs) with start dates occurring any time after receiving the study intervention until 3 days (for non- serious AEs) or 3 days (for SAEs) after the last day of study intervention will be documented.

Participants who are discharged from the ED will receive a survey via email or phone call 72 hours (3 days) after leaving the ED to gather information on any events since leaving the ED.

Participants who are admitted to the hospital for an SAE will be followed for outcome information until resolution or in the opinion of a qualified physician delegate, the participate is stable and does not require further follow-up. These participants will not receive the survey 72 hours (3 days) later.

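### The protocol contradicts itself on 72-hour data for children admitted at the index visit, and its two 72-hour outcomes compare only children sent home, a group that treatment may change

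*Protocol*

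**What the plan says.** **Follow-up of admitted children.** Section 4.2 has the study nurse complete measures up to 180 minutes and then closes the child's participation: "After that, the participant is considered complete. No follow-up will occur 72 hours later". Section 8.1.4 agrees: "If the participant was admitted to the hospital at their index ED visit, they will not be contacted for the follow-up survey". The footnote to the schedule of activities (1.3) also restricts the survey to discharged children.

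**Safety window.** Section 10.3.4 covers all adverse events and serious adverse events "with start dates occurring any time after receiving the study intervention until 3 days" after the intervention. Beyond the survey of discharged children, it names follow-up only for those admitted for a serious adverse event.

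**Chart review.** The schema (1.2) lists "Electronic/paper health chart review and telephone/email follow-up at 72 hrs (+7days"), without saying whether admitted children are included. Section 9.8 describes the 72-hour ascertainment by e-mail and telephone only.

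**ICU.** The trial-specific serious events in section 10.2 are "admission to intensive care unit (ICU) at the index ED visit" and ICU admission for asthma within 72 hours after discharge from the ED.

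**72-hour outcomes.** Section 9.3 lists index hospitalisation first. It then lists hospitalisation within 72 hours of ED discharge and "Unscheduled asthma-related visits to any health care provider within 72 hours post- ED discharge".

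**Tests.** Section 9.7: "For binary outcomes (hospitalization, PRAM indicating mild asthma, unscheduled asthma-related re-visits), groups will be compared using the chi-square test", with an adjusted logistic regression as well. Section 9.9 reports adverse-event frequencies descriptively and adds: "If appropriate, differences between the groups will be compared using a two-sample t-test or Wilcoxon rank sum test".

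**The concern.** There are two separate problems.

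First, the sections disagree about what is known of an admitted child after 180 minutes. A site that follows 4.2 stops there. A site that follows 10.3.4 must record events for 3 days, with no procedure described for doing so unless the admission was itself for a serious adverse event. Section 10.3.3 lists asthma-related hospitalisation among expected events that are not reported, so an ordinary asthma admission does not clearly open that route. The admitted children are the sicker ones. Length of stay (9.3) and the 72-hour economic horizon (9.12, Appendix E) also need their later data.

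Second, the two 72-hour outcomes exist only for children sent home. If magnesium changes who goes home, the discharged groups differ in severity for reasons other than chance, and their relapse rates are no longer a randomised comparison.

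**Working it through.** **1. How many children.** The earlier nebulised-magnesium trial gives 178/409 = 43.5% and 194/407 = 47.7% hospitalised by arm (Appendix A), together 372/816 = 45.6%. Its secondary analysis gives 364/816 = 44.6% (Appendix C). Both agree with the 45% in section 2.2. Applied to 192 children:
- admitted: 192 × 0.446 = 86 to 192 × 0.456 = 88;
- discharged: 106 to 104.

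This is not a planning rate for the present trial. In the same secondary analysis 190/215 = 88.4% of children given open-label IV magnesium were admitted. At that rate only 96 × 0.116 = 11 per arm would go home, but the figure comes from children selected by their physicians for IV magnesium, so it is an outer bound.

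**2. How many events carry the 72-hour comparison.** Section 2.3 cites ED return rates of 13/723 = 1.8% and 1383/38,623 = 3.6%. With about 105 discharged, 105 × 0.018 = 1.9 and 105 × 0.036 = 3.8, so 2 to 4 events in total, or about 1 to 2 per arm. These are registry rates of return to the ED. The trial's outcome, a visit to any provider, may be more frequent.

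**3. ICU.** Section 9.4 cites 19/372 = 5.1% ICU care among hospitalised children. With 45% admitted: 96 × 0.45 × 0.051 = 2.2 per arm. The documents do not say how many of these went through a ward first.

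**4. What the selection can do (assumed rates).** Suppose 55% of children are milder and 45% sicker, with 72-hour relapse of 2% and 10% whatever the treatment. Milder children go home at 80% in both arms; sicker children at 50% on magnesium and 30% on placebo.
- Discharged: magnesium 0.55 × 0.80 + 0.45 × 0.50 = 0.665; placebo 0.55 × 0.80 + 0.45 × 0.30 = 0.575.
- Relapse among discharged: magnesium (0.44 × 0.02 + 0.225 × 0.10)/0.665 = 4.7%; placebo (0.44 × 0.02 + 0.135 × 0.10)/0.575 = 3.9%. Risk ratio 1.21 against magnesium, with no true effect on relapse.
- Hospitalised at index or relapsed, all randomised: magnesium 1 − 0.665 + 0.031 = 36.6%; placebo 1 − 0.575 + 0.022 = 44.7%, in favour of magnesium.

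Across six such settings (discharge raised by 4.5 to 10 points, relapse of 6% or 10% in sicker children) the risk ratio ran from 1.07 to 1.21. Exchanging the arms reverses the direction.

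**5. Missing or undefined.** Section 9.9 imputes missing data by multiple imputation without exception. For an admitted child a post-discharge 72-hour outcome is undefined, not missing, and imputing it would invent a discharge that did not happen.

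**The case against.** **Follow-up may not really stop.** Section 4.2 can be read as ending only nurse measures and the 72-hour contact. Length of stay implies later data, the chart review is not limited to discharged children, and 10.3.4 covers everyone on its face. This stands against any claim that late events would be lost. It does not remove the conflict: to call the matter covered is to prefer the schema and 10.3.4 over 4.2, and the protocol has to make that choice itself.

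**Ward-to-ICU transfer.** A reader might infer that such a transfer could never count as a serious adverse event. The documents do not support that. The general definition in 10.2 includes life-threatening events and those that prolong a stay, and 9.4 collects ICU admissions without naming a route. What stands is that no procedure described for admitted children reliably looks for it.

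**The outcomes are simply defined after discharge, and index admission is compared on its own.** This is fair. It is also too strong to call the comparison a breach of intention-to-treat: section 9.5, where that principle is stated, is headed as the primary efficacy analysis, and no section gives the denominator for these outcomes. The selection remains whatever name it is given. Its size in step 4 is illustrative.

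**The tests.** A reader might infer that a t-test or Wilcoxon test on event frequencies produces false positives. It does not. By full enumeration on 0/1 data, a nominal 5% t-test at 96 per arm has true size 1.2% to 4.8% for event rates of 1% to 6.8%, and 2.6% at 53 per arm with a 2.7% rate. Pearson chi-square gives the same values. Fisher's exact test has size 0.03% to 2.5% and 0.15% respectively, so requiring it would make rare harms harder to detect. Moreover, 9.9 tests only if appropriate, 9.4 names no test, and chi-square is assigned to hospitalisation and re-visits, not to adverse events. What stands is a poor fit of method to proportions with very few events.

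**Conclusion.** The concern holds in two parts. Sections 4.2 and 8.1.4 conflict with 10.3.4, and the schema's chart review does not resolve the conflict because its scope is unstated. If 4.2 is followed, 72-hour safety and resource data are incomplete for about 45% of children (about 87 of 192), assuming admission as in the earlier trial; the share could be higher. The two 72-hour outcomes condition on a secondary outcome that treatment may change, and would rest on about 105 children and 2 to 4 events at the cited return rates. In the assumed settings above, selection alone shifted the risk ratio by 7% to 21%.

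The test wording is a minor matter of specification, not of error control. The primary endpoint, PRAM at 120 minutes, is untouched, and so is the de-implementation decision in section 2.1 so far as it rests on respiratory distress. The change is worth making because it is cheap and affects the trial's 72-hour safety record and several secondary outcomes.

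**What to change.** 1. Reconcile 4.2 and 8.1.4 with 10.3.4 and the schema. State that the 72-hour chart review covers children admitted at the index visit, and that adverse events, serious adverse events and ICU admission by any route, ward transfer included, are recorded to 72 hours for all randomised children.
2. Add to 9.3 an all-randomised outcome: hospitalised for asthma at the index visit or within 72 hours of ED discharge. Do likewise for index admission or unscheduled visit. Show the components, give discharged-only rates descriptively, and exclude post-discharge outcomes of admitted children from multiple imputation.
3. In 9.7 and 9.9, report adverse-event and 72-hour event proportions with risk differences and exact or score confidence intervals, in place of a t-test or Wilcoxon test on frequencies. No particular significance test need be required.

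The cost is a short chart review for about 87 children, in a trial whose schema already lists chart review, plus protocol wording. The composite will be dominated by index admission (about 87 children against 2 to 4 later events), which is why its components must be shown.
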